### Independent variables

The primary exposure variable of interest is the intervention, i.e. the implementation of the “In-HospiTOOL”. As outlined in the statistical plan, we will adjust our model to the following covariates: demographics (age, gender, health care insurance, home of residence [home versus facility]), main diagnosis (grouped using the “International Classification of Diseases (ICD-10)” [24]), comorbidities (using the Elixhauser comorbidity index [19]), and study center.

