### Challenges and current evidence

Misutilization and suboptimal resource allocation challenges safe and efficient, patient-centered in-hospital transition from the emergency department (ED) to a medical ward, and transition to home or post-acute care facilities [5]. Errors that lead to unplanned readmissions and preventable deaths are more common in polymorbid patients [6]. Since the majority of medical inpatients with chronic illnesses become hospitalized via ED (non-electively), optimized resource use must start at the ED with an improved triage.

The optimal organization of routine medical ward care in mostly polymorbid, elderly medical patients received less alertness than the handling of specific diseases. Specifically, there is a lack of large trials focusing on polymorbid patients and their objective outcomes [7]. The inter-professional team care approach with a comprehensive geriatric in-hospital assessment has been found effective to increase patients’ likelihood of being alive and living in their own homes after an emergency admission to hospital [8]. Conversely, many earlier studies were unable to link interdisciplinary team care interventions to affect existing metrics, partly because of limited methodology and outcome measures [9]. As recently shown in a review article, several innovative interprofessional and interdisciplinary healthcare interventions on medical wards usually have chosen length of hospital stay, mortality rates, readmission, or functionality as their primary outcome measures [10]. However, most interventions have not shown any effect on these patient-oriented outcomes and are therefore debatable and inconsistent. Few evidence suggests that an improved interprofessional collaboration would reduce adverse effects of care. Thus, a significant reduction in length of hospital stay have been reported due to contemporaneous secular reasons [11], which most of the published interventions did not reduce additionally. The majority of inpatient setting interventions were unlikely to reduce readmissions, neither to reduce mortality rates, nor to diminish need for nursing facilities after discharge. However, generalizability of these findings remains weak due to discrepancies between different healthcare systems and heterogeneous (inter-)national standards of care.

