### Setting, study sites and characteristics of participants

The multicenter trial includes seven secondary and tertiary care hospitals within Northern Switzerland. This allows to collect representative nation-wide patient-oriented data from polymorbid patients. All senior executive leaders have reassured full support for an optimal implementation of the “In-HospiTOOL” in their hospitals. Upon hospital admission, consecutive adult (age ≥ 18 years), polymorbid (> 1 diagnose) medical inpatients will be included in our study. Except for non-medical and non-adult patients there will be no exclusion criteria.

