#### Control population

For our statistical approach as outlined below, we request data from the Federal Statistical Office to provide a nationwide comparability. We will use data on length of hospital stay. Age, gender, health care insurance, place of residence, main diagnosis, comorbidities, and study center will be used for statistical adjustment.

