### Theoretical aspects, hypothesis

#### Module 1 resource (mis-)utilization & allocation

We hypothesize that implementing the “In-HospiTOOL” in a nationwide multicenter setting will significantly shorten length of hospital stay without compromising patient outcomes and functional independence. Systematic early determination of clinical stability, estimation of the post-acute care referral probability (using the Post-acute care discharge [PACD] score [15]), fixing a possible discharge date after initial ED assessment as well as a tight interprofessional collaboration enabled through an electronical communication platform (“Visitentool”, Fig. 1) will result in decreased waiting times contributing to the shortening of length of hospital stay [16–18].

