**Fig. 2 Fig2:**
[figure not shown]
The “In-HospiTOOL”. An integrative patient management tool. The “In-HospiTOOL” has three components involving admission (inter-professional initial assessment, *“Ersterfassung”*), medical ward (inter-professional daily re-assessment, *“Visitentool”*), and discharge (inter-professional patient education, reengineered discharge [32]). PACD, Post-Acute Care Discharge [15, 18]

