### Statistical analysis plan and sample size

The primary analysis population includes all consecutively recruited patients following an intention-to treat (ITT) principle. The number of patients lost to follow-up will be minimized by every effort. The per-protocol (PP) population analysis will be prospectively defined to exclude patients in whom major protocol violations have occurred. Specifically, the following criteria will lead to exclusion from the PP population: major violation of study inclusion or study exclusion criteria, patients with missing information from the In-HospiTOOL forms, or missing follow-up interviews.

We will compare all endpoints between all three study phases in the overall ITT population, the PP population and within predefined subgroups as discussed below. We will analyze all endpoints in an adjusted manner for the main covariates such as age, gender, health care insurance, home of residence, main diagnosis, comorbidities, and study center. Regarding sample size considerations, we include consecutive patients in each hospital over a 6-month period for the observation, implementation, and the intervention period, respectively. Given the large number of patients per study site seen in routine (i.e. between 2`500 and 8`000 polymorbid medical inpatients) per year, we estimate to enroll approximately ~ 35′000 patients over 18 months of recruitment. This large amount of patient data will provide adequate power to investigate the effect of introducing a patient care tool in the overall medical hospitalized patient population and allow for subgroup analyses, as well as important post-hoc analyses.

We will perform two complementary, quasi-experimental analyses to estimate the effect of the intervention: difference in differences and ITS.

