#### Difference in differences

To quantify an overall effect on length of hospital stay after implementing the “In-HospiTOOL”, we fit a patient-level multivariate linear regression model. It will include lengths of hospital stay of “control” hospitals, all risk adjusters listed above in the manuscript, and a time variable for study weeks. The dependent variable will be length of hospital stay (days in hospital). We will test for interaction between the intervention period and the intervention population and will assess whether there is a difference in the change (slope) in length of hospital stay over time between the two study populations. The intervention and control groups will have different baseline characteristics, however both groups will be exposed to similar alterations in outcomes over time without the interventional program.

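### The named adjusters leave out emergency versus elective admission, so a change in admission mix that differs between trial and control hospitals could be read as a tool effect

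*Protocol article*

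**What the plan says.** The protocol article names its adjusters in three places.

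- Independent variables: "we will adjust our model to the following covariates: demographics (age, gender, health care insurance, home of residence [home versus facility", followed by ICD-10-grouped diagnosis, the Elixhauser index and hospital.
- Control population: "Age, gender, health care insurance, place of residence, main diagnosis, comorbidities, and study center will be used for statistical adjustment".
- Statistical analysis plan and sample size: "We will analyze all endpoints in an adjusted manner for the main covariates such as age, gender, health care insurance", then the remaining items of the same set.

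None of the three includes admission route. The Difference in differences section enters "all risk adjusters listed above in the manuscript, and a time variable for study weeks". The Interrupted time series section likewise refers back to the risk factors already named when it describes the weekly adjusted stay.

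Elective admissions are not screened out. Beyond the requirement of more than one diagnosis, the Setting section says "Except for non-medical and non-adult patients there will be no exclusion criteria". The Background treats route as relevant to these patients: "the majority of medical inpatients with chronic illnesses become hospitalized via ED (non-electively". A majority is not all, and no share is given.

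**The concern.** The effect estimate is the interaction between intervention period and intervention population. The Difference in differences section accepts that the two groups differ at baseline and relies on their outcomes changing alike over time had there been no intervention. Admission route can threaten that reliance: if emergency and elective patients differ in stay, and the emergency share drifts differently in the seven hospitals than in the controls, the interaction term picks up the drift.

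If emergency patients stay longer (an assumption), a fall in emergency share confined to the trial hospitals would look like the hoped-for shortening, and a rise would hide a real one. The large sample does not protect against this, since it shrinks the standard error and not the bias. The time-series sensitivity analysis does not protect either, since it uses the same adjusters.

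**Working it through.** **Figures in the article.** There is no power calculation to reproduce: alpha, power, target difference and standard deviation (SD) of stay are not given. The only sample-size figure is about 35,000 patients over 18 months. Seven sites at 2,500 to 8,000 per year give 7 × 2,500 × 1.5 = 26,250 to 7 × 8,000 × 1.5 = 84,000. One site at 8,000 and six at 2,500 give (8,000 + 6 × 2,500) × 1.5 = 34,500, so 35,000 is compatible, at the low end. Equal phases give 35,000 / 3 ≈ 11,667 patients each. This count is used below only for scale.

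**Assumed inputs.** The article supplies none of these:

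- g, the gap in mean stay (emergency minus elective) left after the listed adjusters: 0.5 to 3 days, taken as equal in both groups and periods;
- the differential shift in emergency share: 1 to 10 percentage points;
- the SD of stay: 5 to 9 days.

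**Formula.** Bias of the interaction = g × [(change in emergency share, trial) − (change in emergency share, control)].

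**Results with g = 2 days.**

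- Stable difference, 85% trial and 70% control in both periods: 2 × (0 − 0) = 0.
- Common shift, 85% to 90% and 70% to 75%: 2 × (0.05 − 0.05) = 0.
- Differential shift, 85% to 80% in trial hospitals, control constant at 70%: 2 × (−0.05 − 0) = −0.10 day.

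Over the full assumed ranges the absolute bias runs from 0.5 × 0.01 = 0.005 day to 3 × 0.10 = 0.30 day.

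**Check by simulation.** Patient-level regressions were run with no true effect (100 runs, 11,667 patients per cell, SD 7 days, g = 2).

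| Scenario | Interaction without route | With route |
|---|---|---|
| Stable difference (85% vs 70%) | −0.001 day | −0.002 day |
| 5-point fall, trial hospitals only | −0.099 day | 0.002 day |

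The route term removes the bias where there is one and changes nothing where there is none.

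**Scale.** The standard error of the trial-side before-after difference is SD × √(2/11,667), which is 0.065 day at SD 5 and 0.118 day at SD 9. A bias of 0.10 day is thus about 0.8 to 1.5 standard errors. This ignores control variance and clustering. With a control group of equal size the standard error is SD × √(4/11,667) = 0.093 to 0.167 day, and 0.10 day is about 0.6 to 1.1 of it. Variation between hospitals would lower these ratios further.

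**Precision.** The variance explained by route is p(1 − p)g²/SD². With g = 2, SD 7 and an assumed elective share p of 10% to 20%, this is 0.09 × 4/49 = 0.7% to 0.16 × 4/49 = 1.3%. The gain is slight.

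**The case against.** The strongest reply is that this is a condensed article. One list is introduced openly ("We will analyze all endpoints in an adjusted manner for the main covariates such as age, gender, health care insurance"), the Independent variables section points to a statistical plan, and a fuller plan could add route. It is fair to say that the list is not strictly closed. But the article does name a set, three times and consistently, and the difference-in-differences model is tied to what is listed in the manuscript itself. As written, route is not in either model.

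Three stronger readings are tempting, and the document does not support them.

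- A reader might infer that unequal admission mix between trial and control hospitals is itself a source of bias. It is not, because a stable difference cancels.
- A reader might blame where the tool acts, because one element is "fixing a possible discharge date after initial ED assessment". The figure legend on the tool, however, speaks of "three components involving admission (inter-professional initial assessment", and nothing says that elective patients skip that step. Different exposure by route would dilute or modify the effect; it would not confound the interaction.
- A reader might conclude that a mix shift will be reported as a tool effect. The article gives no sign of any such shift, and the observation and intervention phases are season-matched, which limits one obvious cause.

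It also stands that diagnosis, comorbidity, residence and hospital absorb part of the emergency-elective gap, so only the remainder counts. Finally, the document does not say whether the Federal Statistical Office data record admission route.

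**Conclusion.** The point holds in a limited form. Admission route is absent from every list of adjusters and so from both models, while elective patients are eligible. The length-of-stay estimate is exposed only to a change in emergency share that differs between trial and control hospitals and is not captured by the listed adjusters. The size is about 0.10 day under a 2-day residual gap and a 5-point differential shift, and from near 0 to about 0.3 day over the assumed ranges. Gap, shift and SD are all assumptions, so these figures show that the bias could be comparable with the standard error, not that it is.

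Comparisons between phases within the trial hospitals alone have no control group to cancel even a common shift. This could apply to the interview-based endpoints, since length of stay is the only control outcome that the Control population section names.

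This is a worthwhile, inexpensive improvement to the adjustment set, not a flaw that invalidates the design.

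**What to change.** Add admission route (emergency versus elective) to the covariates in the Control population, Independent variables and Statistical analysis plan sections. Request the field from the Federal Statistical Office, and include it in the difference-in-differences model and in the weekly risk adjustment for the time series.

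The cost is one more field in the control request and one more model term. The sites very likely hold route already, because delays in emergency-department flow and satisfaction with that department are endpoints; this is an inference, as the article does not say so.

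The downside is that the control data may not carry the field. In that case, adjust for route in the phase comparisons within the trial hospitals, report their elective share by phase, and state plainly that the trial-versus-control contrast is not adjusted for admission route.

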### Data collection process

The study period is divided into three 6-month phases, whereas the observation and the intervention phase until the end of January 2019 are season-matched, interrupted by a run-in non-season-matched implementation phase. The period of “In-HospiTOOL” implementation in the participating hospitals will be devoted to technical implementation, training of involved study personnel, nurses, social workers, physicians, and pilot testing. We will collect data throughout all three study periods by using electronic medical records and will contact all patients 30 days after hospital admission by phone interview. Data from the structured phone interviews will be stored on a data base using the secuTrial© software (secuTrial®; interActive Systems GmbH, Berlin, Germany).

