#### Interrupted time series (ITS) model

We will analyze the trends in length of hospital stay from start of observation through the end of the intervention period (18 months). For this purpose, we will conduct an ITS as a sensitivity analysis. We will implement the ITS using generalized estimating equations (GEE), to examine linear trends in weekly, hospital-level, risk-adjusted length of hospital stays. ITS models will be tested for autocorrelation to control for seasonal trends using the Durbin-Watson statistics [25]. We will analyze the change in trend between all three time periods. This approach allows us to distinguish between a possible effect of the intervention and a difference from underlying trends facing both study groups and can also help to analyse whether the intervention effects will sustain over time. We will calculate weekly-adjusted length of hospital stay using linear GEE that includes all lengths of hospital stay from the control and intervention populations and all above mentioned risk factors. We will graph weekly length of hospital stay for all populations over time and use the estimated weekly means for control and intervention patients to assess for a weekly difference between the two groups. Finally, we explore whether the adjusted weekly length of hospital stay decreases in the intervention period and whether there will be an independent time trend effect induced by the intervention only [26].

To summarize, we will use four statistically hypothesis tests during each period: (i) Are there significant trends in length of hospital stay change during the period. (ii) Will the trend differ between the control and intervention populations (the interaction between time and control or intervention conditions) during the period. (iii) Will the trend during the intervention period differ from the trend during the observation period within all three conditions. (iiii) Will the magnitude of the altered trend between the intervention and the observation period differ between the three conditions (the interaction between the change in slope and intervention or control conditions). These models will also be implemented for the analyses of the secondary endpoints.

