Our study has several potential limitations. First, inclusion of about 35`000 patients over the 18-month study time frame is ambitious. However, based on our large experience from previous multicenter studies, a well-established multicenter research network, and the high prevalence of hospitalized multimorbid patients eligible for this trial, we are convinced that the trial is feasible. The second limitation of this trial is the lack of randomization. Methodologically, in a trial whose intervention focuses on the process of care, neither patient-level randomization nor a randomized cross-over design was feasible as a carry-over effect would have biased the control group. For a cluster randomized trial, a large number of similar clusters (i.e. hospitals) would be needed – which is challenging in Switzerland particularly in light of the limited study budget. Therefore, we chose an ITS model in a quasi-experimental study design using administrative data from non-participating hospitals as a control group. Doing so, we account for differences in the patient population that may occur due to epidemiological variations. Third, as a pragmatic trial with a bundled intervention, it will be challenging to understand which part of our intervention shows clinical effects, leading to potential participation bias. Nonetheless, the large amount of health care data collected will also allow to provide scientific evidence as to which elements of patient management are influenced by the intervention.

In conclusion, this pragmatic comparative effectiveness health services research trial will inform whether the implementation of a novel electronic tool for inpatient management optimizes inter-professional collaboration and thereby reduces length of hospital stay without derogating subjective and objective patient-oriented measures. Our trial will help to compare between diverse transition processes within seven different hospitals and to create a benchmarking for inpatient care quality. This study synergizes national networks and, thus, has the potential to become a cornerstone in the present public healthcare discussion.

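### Every effect estimate is adjusted for diagnosis codes that apparently come from the stay being analysed, and nothing described would show whether fuller recording in the tool hospitals produced part of a reduction in stay.

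*Protocol article*

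**What the plan says.** The section on independent variables lists the adjusters: age, gender, insurance, residence (home or facility), ICD-10 main diagnosis, "comorbidities (using the Elixhauser comorbidity index [19]), and study center". The statistical section applies them throughout: "We will analyze all endpoints in an adjusted manner for the main covariates". The difference-in-differences model takes "all risk adjusters listed above in the manuscript, and a time variable for study weeks". The interrupted time series, which is the sensitivity analysis, uses GEE "to examine linear trends in weekly, hospital-level, risk-adjusted length of hospital stays". No estimate without the coded diagnoses is described.

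On sources, the control data are requested from the Federal Statistical Office, and "main diagnosis, comorbidities, and study center will be used for statistical adjustment". The limitations paragraph of the Discussion describes the design as "using administrative data from non-participating hospitals as a control group". For the study hospitals, the data collection section says: "We will collect data throughout all three study periods by using electronic medical records". The article mentions no present-on-admission restriction and no look-back to earlier stays.

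The Fig. 2 legend gives the tool "three components involving admission (inter-professional initial assessment", followed by daily re-assessment on the ward and patient education at discharge. The Coaching section adds a local supervisor who monitors use of the physician's initial assessment, the PACD score, the ward-round tool and the discharge form.

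**The concern.** A covariate protects a non-randomised comparison only if the exposure does not change it. A comorbidity index built from codes of the current stay reflects both how ill the patient is and how thoroughly the stay was documented. A structured multi-professional assessment at admission and every day could plausibly make documentation fuller. That would happen in one population and one period, which is exactly the contrast that the period-by-population interaction estimates. Center effects absorb only constant differences between hospitals, and controls absorb only changes that they share.

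The difference-in-differences section assumes similar changes in outcomes in both groups in the absence of the programme. It says nothing about trends in recorded covariates. The time-series analysis is risk-adjusted in the same way, so it would reproduce the problem rather than reveal it. At stake is whether a lower adjusted stay means earlier discharge or better documentation.

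**Working it through.** **Inputs from the document.** About 35,000 patients over three 6-month phases at seven hospitals, each with 2,500 to 8,000 eligible patients a year. The site volumes give 7 × 2,500 × 1.5 = 26,250 to 7 × 8,000 × 1.5 = 84,000. The stated total lies inside this range, and an even split gives 35,000 / 3 ≈ 11,667 per phase. The article states no effect size, SD, alpha or numerical power, so there is no power figure to reproduce.

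**Assumed inputs.** Days of stay per recorded condition, β = 0.7 to 0.8. Extra recorded conditions per stay, in the tool hospitals after the tool starts, δ = 0.1 to 0.3. SD of stay 5 to 8 days. Two-sided alpha 0.05.

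**Fuller recording, no true effect.** If the recorded count equals the true count plus δ in the exposed cell only, then bias in the adjusted interaction = −β × δ. This gives −0.7 × 0.1 = −0.07 days at the low end and −0.8 × 0.3 = −0.24 days at the high end. Two simulated difference-in-differences regressions agree:

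| δ | β = 0.7: adjusted minus unadjusted | β = 0.8: same-stay-adjusted minus baseline-adjusted |
|---|---|---|
| 0.1 | −0.08 | −0.056 − 0.023 = −0.08 |
| 0.2 | −0.15 | −0.134 − 0.023 = −0.16 |
| 0.3 | −0.22 | −0.239 − (−0.008) = −0.23 |

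With δ = 0 and no codes accruing during the stay, adjusting for the recorded count and for the baseline count gives the same estimate (0.006 for both).

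**Comparison with precision.** For two phases of 11,667, ignoring clustering, SE = SD × √(2/11,667). At SD 6 this is 0.0786. The difference detectable with 80% power is (1.96 + 0.84) × 0.0786 ≈ 0.22 days; it is 0.18 at SD 5 and 0.29 at SD 8. A pure bias of 0.1 days would be declared significant in 33%, 25% and 16% of trials at SD 5, 6 and 8. A bias of 0.2 days would be declared significant in 86%, 72% and 48%. Clustering would lower these percentages but would not shrink the bias.

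**Shorter stay, fewer codes.** This is the opposite mechanism. With a true effect of −0.5 days and conditions accruing at 0.05 or 0.10 per day in hospital, the estimate moves from −0.492 to −0.469 (1 − 0.469/0.492 ≈ 5%) or from −0.491 to −0.446 (about 9%). With no true effect and accrual of 0.10 per day, the two adjustments differ by 0.001 days. This mechanism slightly dilutes a true effect and does not create one.

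**Can a shift be seen?** In the simulation with β = 0.7 and an assumed 120,000 controls per phase, the same model with recorded comorbidity as outcome gave t = 4.7, 8.9 and 13.1 for δ = 0.1, 0.2 and 0.3. These values also ignore clustering.

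**The case against.** The strongest reply is that the premises are inferred. No section says that the codes belong to the analysed stay. Their source and timing may be set out in a full protocol or analysis plan that is not shown. The tool is described in terms of clinical stability, PACD score, discharge dates, reasons for delay and discharge education, with no coding function. The magnitudes are products of two assumed numbers, so the simulation confirms the algebra and not the occurrence. Case-mix adjustment is also needed: the trial is not randomised, and the article expects the groups to differ at baseline.

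Most of this stands, and it limits the point. A reader might infer that the primary estimate is biased, or that the tool is known to change coding; the document supports neither. A reader might also infer that the bias could run strongly either way, but the shorter-stay mechanism only dilutes a true effect, by about 5 to 9% in the scenarios tried. Nor does the document show that the same codes decide eligibility. Inclusion requires more than one diagnosis but takes place at admission, and the article does not tie it to the codes used for adjustment.

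The silence on timing does not dispose of the matter. The commitment to adjust every endpoint in both models is in the article itself. Administrative control records enter the same model, which makes episode coding much the likeliest source.

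**Conclusion.** The point holds conditionally. The adjustment is defensible, but the plan describes nothing that would tell a real reduction in stay from a change in recording. If recording became fuller in the tool hospitals only, the adjusted interaction would show a spurious reduction. It is about 0.08 to 0.23 days for 0.1 to 0.3 extra recorded conditions at 0.7 to 0.8 days each, of the same order as the smallest effect the trial could detect. The result rests on three assumptions: same-stay coding, a differential recording shift, and the assumed days per condition. The first is the natural reading, the second is plausible but not documented, and the third is illustrative. This is a cheap and worthwhile improvement, not a demonstrated error.

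**What to change.** Keep the planned case-mix-adjusted model as primary and pre-specify two additions:

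1. Fit the same difference-in-differences model with the recorded Elixhauser score as outcome.
2. Report the effect on length of stay side by side with and without the coded diagnoses. The second version adjusts only for age, gender, insurance, residence before admission and center.

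Neither estimate should replace the other automatically, because the first check cannot tell a recording change from a genuine change in case mix. If the score moves differentially and the two estimates diverge, state that the reduction cannot be separated from a change in recording or in case mix.

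The cost is analysis-plan wording and two extra model fits on data already planned. The reduced model has slightly wider intervals and gives less protection against a real case-mix shift, which is why it accompanies the primary model and does not replace it.
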